#### MDT

Ideally, patients will be discussed in a first MDT after initial staging with gastroscopy and CT of the thorax and abdomen, and in a second MDT after additional staging with PET and SL (Fig. 1). In practice, in some patients the first or second MDT will be skipped and patients will proceed to additional staging or treatment without intervention of MDT’s. An included patient should be discussed in at least one MDT. Occasionally, an additional diagnostic modality will be required and the patient is discussed during a third MDT.

#### Treatment

If the tumor is deemed to be resectable, patients will be scheduled for treatment. Treatment will not be initiated before completion of staging according to the Dutch guidelines, including PET and SL [15]. There are no additional restrictions to the further treatment strategy, such as chemotherapy regimen or type/approach of resection.

### Outcome measurements

The primary outcome of this study is the proportion of patients in whom PET and/or SL leads to a change in treatment strategy. This includes the proportion of patients in whom surgery with curative intent is prevented, and the proportion of patients in whom the chemotherapy regimen is changed or omitted. Secondary outcome parameters include cost-effectiveness, modality-specific performances (diagnostic performance of both modalities, incidental findings on PET), patients’ extra burden of the diagnostic modalities (morbidity and mortality, diagnostic delay, number of extra MDT’s held), and overall quality of life of patients (EORTC Quality of Life questionnaires).

### Sample size calculation

Based on previous literature it is expected that 27% of patients will have a change in treatment strategy [11]. Taking a safety margin of 5% into account (thus at least 22% of patients will have a change in treatment strategy), an alpha of 0.05 and a power of 0.80, at least 239 patients need to be included in this study to demonstrate that performing a combination of both diagnostic modalities is cost-effective. Based on the yearly number of gastrectomies performed in the participating centers, approximately 543 patients are expected to be eligible for the study in 36 months.

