**Methods:**

This prospective observational cohort study will include all patients with a surgically resectable, advanced gastric adenocarcinoma (cT3–4b, N0–3, M0), that are scheduled for treatment with curative intent after initial staging with gastroscopy and CT. The modalities to be investigated in this study is the addition of PET and SL. The primary outcome of this study is the proportion of patients in whom the PET or SL lead to a change in treatment strategy. Secondary outcome parameters are: diagnostic performance, morbidity and mortality, quality of life, and cost-effectiveness of these additional diagnostic modalities. The study recently started in August 2017 with a duration of 36 months. At least 239 patients need to be included in this study to demonstrate that the diagnostic modalities are break-even. Based on the annual number of gastrectomies in the participating centers, it is estimated that approximately 543 patients are included in this study.

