## Background

Gastric cancer is the fifth most common type of cancer worldwide [1]. In Western countries, curative treatment consists of gastrectomy with perioperative chemotherapy [2–4]. Unfortunately, the prognosis of patients who undergo curative treatment remains relatively poor, with a 5-year overall survival rate of 20–40%. The main cause for this poor prognosis is tumor recurrence [2, 5]*.* The poor prognosis, treatment-related morbidity and mortality, and impairments in quality of life result in a high disease burden [6].

The standard diagnostic work-up of patients with gastric cancer includes a gastroscopy to assess tumor size and location and to obtain tissue to characterize the tumor. Furthermore, computed tomography (CT) of the thorax and abdomen is performed to detect metastases and evaluate local resectability. However, the accuracy of CT for detecting metastatic disease (M1) or local irresectability (T4b) is low: the sensitivity to detect peritoneal metastases is 22%–33%, to detect distant metastases is 14%–65% and to detect T4b disease is 5%–69% [7–10]. Consequently, two undesirable situations may occur in practice:

1. Unexpected intraoperative peritoneal metastases or local tumor irresectability are found at the onset of gastrectomy.

2. Undetected distant metastases presenting shortly after treatment with curative intent (neoadjuvant chemotherapy and/or surgery).

In both situations, patients undergo a futile treatment, probably leading to a reduced quality of life and an increase in health care costs.

A recent study from the United States investigated the additional staging capacities of fluorodeoxyglucose positron emission tomography with CT (PET) and staging laparoscopy (SL) in gastric cancer. In this study, combination of PET and SL identified additional metastases in 27% of patients: distant metastases by PET in 10% of patients, and peritoneal metastases by SL in 19% of patients (with an overlap of 2%) [11]*.*To reduce the number of patients undergoing futile treatment, the new Dutch guidelines for the treatment of gastric cancer recently included PET and SL in the staging algorithm of locally advanced (cT3–4) tumors“(http://www.oncoline.nl/maagcarcinoom)”. However, this guideline concludes that the evidence for both staging modalities is weak, and additional studies are needed to further investigate the cost-effectiveness and applicability of routinely adding PET and SL to the staging of locally advanced gastric cancer.

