In this study, patients will first undergo a PET, followed by a SL if PET does not show distant metastases. If distant metastases found on PET are confirmed by biopsy or additional imaging, SL will be omitted. This order was chosen as it is more applicable in clinical practice for the following reasons:PET is non-invasive, whereas a SL is invasive and is accompanied by a higher risk of adverse events for the patients.Assessing the PET after SL will be less reliable, due to uptake of FDG in postoperative inflammation.PET scans can be scheduled more easily and probably results in less diagnostic delay.In a theoretical model from a previous study, first performing PET resulted in more cost savings compared to a SL-first approach (difference $2168 per patient) [11].

This study aims to include patients with locally advanced (cT3–4) gastric cancer, but the accuracy of CT for determining T-stage is low [8]. This could result in the unintended inclusion of early stage (T2) tumors or failure to include truly advanced tumors. Nevertheless, these flaws reflect current practice. To reduce the impact of these current limitations, an expert panel will review all CT-scans to reach consensus on the clinical T-stage as a side study.

The current study is relevant, as the addition of PET and SL may prevent futile gastrectomies, which are associated with considerable morbidity, mortality, reduction in quality of life and costs [28–30]. On the other hand, the number of prevented gastrectomies should exceed a certain level, as PET and SL are accompanied by costs and possible risks for the patient (ionizing radiation, surgical complications) as well. The results of this study will be implemented in an updated version of the Dutch guidelines, but may also be applicable to all other Western countries with comparable treatment algorithms and health care systems.

By performing staging laparoscopy before starting treatment, a side effect of this study might be that more patients with peritoneal carcinomatosis will be detected. Recent studies have shown that there may be a role for hyperthermic intraperitoneal chemotherapy (HIPEC) and cytoreductive surgery in these patients [31, 32]. Patients with peritoneal carcinomatosis as detected in this study may therefore be included in HIPEC trials [33].

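### Exceeding 22% on the composite primary outcome cannot by itself show break-even or cost-effectiveness, yet the sample-size rationale says that it will

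*Protocol article*

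**What the plan says.** The Sample size calculation starts from the literature: "it is expected that 27% of patients will have a change in treatment strategy". It then sets the floor: "Taking a safety margin of 5% into account (thus at least 22% of patients will have a change in treatment strategy". With "an alpha of 0.05 and a power of 0.80" it arrives at 239 patients, and gives their purpose as demonstrating that the combination of PET and staging laparoscopy (SL) is cost-effective. The Methods paragraph of the Abstract gives the same 239 a different purpose: "to demonstrate that the diagnostic modalities are break-even".

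Three other places bear on this:

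- **Background**, on the source of the 27%: "combination of PET and SL identified additional metastases in 27% of patients".
- **Outcome measurements**: the primary outcome counts patients in whom curative-intent surgery is prevented, and also "the proportion of patients in whom the chemotherapy regimen is changed or omitted".
- **Discussion**, on what has to offset the costs: "the number of prevented gastrectomies should exceed a certain level, as PET and SL are accompanied by costs". The level is not given.

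The Statistical analysis section reports the primary outcome as a percentage. Separately, it plans a cost-effectiveness calculation, a decision model against CT alone, and a budget impact analysis.

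**The concern.** The sample-size text attaches an economic conclusion to a clinical proportion. That works only if the floor is the proportion at which savings equal costs, and if every counted event carries the saving assumed for it. The article shows neither. It also uses three different quantities as if they were one: metastases found, any change of strategy, and gastrectomy prevented.

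At stake is the conclusion drawn from the primary outcome. A composite above 22% could be reported as proof of break-even when the work-up costs more than it saves, and a composite below 22% could be read as failure when it saves money. The Discussion says that the results will enter an updated Dutch guideline, so the inference matters beyond the paper.

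**Working it through.** **1. The plan's own figures.** From the Background: 10% (PET) + 19% (SL) − 2% (overlap) = 27% with additional metastases. From the Sample size calculation: 27% − 5% = 22%. Both reproduce, and no cost appears in either step.

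The 239 does not reproduce. Take a one-sample test with p0 = 0.22, p1 = 0.27 and power 0.80; the article does not say whether alpha 0.05 is one- or two-sided.

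n = (z_α·√(p0(1−p0)) + z_β·√(p1(1−p1)))² / (p1−p0)²

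- One-sided: (1.645 × 0.4142 + 0.842 × 0.4440)² / 0.0025 ≈ 445.2, so 446.
- Two-sided: (1.960 × 0.4142 + 0.842 × 0.4440)² / 0.0025 ≈ 562.2, so 563.

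This is a separate question and the present point does not rest on it. It matters only for how 239 is described after the correction.

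**2. What a break-even proportion needs.** Let C be the cost per staged patient (PET, SL, their complications, false-positive work-up) and S the net cost saved per patient whose treatment changes. Net saving per staged patient is p·S − C, which is zero at p* = C/S. The article gives neither C nor S. Its one euro figure for this study, €916,438 a year for the Netherlands, is tied to 27%, not to 22%, and one total cannot identify two unknowns.

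For assumed ratios C/S of 0.10, 0.20, 0.25 and 0.30, p* is 10%, 20%, 25% and 30%. This restates the assumption and is not an estimate. It shows that 22% is break-even only if C/S happens to be 0.22: below that ratio the floor is stricter than break-even, above it laxer.

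**3. Which event is counted.**

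| Place | Quantity |
|---|---|
| Background | additional metastases found (27%) |
| Sample size calculation, Outcome measurements | any change: curative surgery prevented, or chemotherapy changed or omitted |
| Discussion | gastrectomies prevented |

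The article does not give the share of changes that are prevented surgery. On assumed shares:

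| Share that is prevented surgery | Prevented surgery when the composite is 22% |
|---|---|
| 100% | 22.0% |
| 80% | 0.80 × 22% = 17.6% |
| 60% | 0.60 × 22% = 13.2% |
| 50% | 0.50 × 22% = 11.0% |

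The same composite covers a twofold range in the event that the Discussion links to cost.

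**4. With components separated.** Put each patient in one category: surgery prevented (s), chemotherapy omitted with surgery kept (o), or chemotherapy changed with surgery kept (c). Then

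net saving = p_s·S_s + p_o·S_o + p_c·S_c − C.

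Two cohorts with the same total p_s + p_o + p_c = 22% have the same net saving only if their mix is the same or the three savings are equal. The break-even level for prevented surgery is

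p_s* = (C − p_o·S_o − p_c·S_c) / S_s,

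which depends on costs and on the other components, not on 27% − 5%.

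**5. Two different claims.** Break-even concerns costs alone. Cost-effectiveness weighs costs against health effects. No single floor on a proportion of changed strategies delivers both.

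**The case against.** The strongest reply is that the economic question is already handled properly. The Statistical analysis section states no decision rule at 22%. It reports the primary outcome as a percentage and judges cost-effectiveness with a model that takes in complications and false-positive PET findings. That stands, and it limits the point: the planned analysis can answer the question. It does not rescue the statement that 239 patients and a 22% floor demonstrate the answer, because the model does not use that floor.

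Several stronger readings are tempting, but the document does not support them.

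- **The 22% is arbitrary, or no cost ever entered it.** An annual saving stated to the euro suggests that some cost calculation exists, and the decision-tree figure is not shown. What can be said is that the article gives no cost rationale and states the derivation as a subtraction.
- **The study will pass or fail at 22%.** No such rule is written. Nor would an observed 23% pass a test: one-sided at 5% with n = 239, about 22% + 1.645 × √(0.22 × 0.78/239) = 26.4% is needed.
- **Only prevented gastrectomies save money, so chemotherapy changes should not count.** The Background includes neoadjuvant chemotherapy in futile treatment, and the Objectives attribute the saving to less futile treatment. Omitted chemotherapy can save cost.
- **Referral to HIPEC trials inflates the outcome and raises cost.** The Discussion mentions this only as a possibility, with no number or cost, and does not say that it counts as a change.

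It can also be said that 27% is a reasonable proxy. In patients selected as M0, newly found metastases are the expected reason to abandon curative surgery. That is fair for planning, but it does not make the three quantities equal.

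**Conclusion.** The point holds as a fault in the stated inference. The Abstract and the Sample size calculation give the primary outcome a property that it does not have: exceeding 22% on this composite cannot by itself show break-even or cost-effectiveness.

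The size of the error in euros or percentage points cannot be determined from the article, which gives neither cost term nor the mix of components. The 22% to 11% range for prevented surgery rests on assumed shares of 100% to 50%, and the 10% to 30% range for break-even rests on assumed cost ratios. The conclusion depends on neither range, only on the absence of a stated link between the floor and cost, and on the mismatch between the composite and the event that the Discussion names.

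**What to change.** 1. Remove from the Abstract and the Sample size calculation the claim that 239 patients demonstrate break-even or cost-effectiveness. Describe 239 only as the size for estimating or testing the proportion with a change in strategy, and say which. If testing 27% against 22% is meant, the number needs its own check (step 1 of the working).
2. State that the cost conclusion rests on the decision model in the Statistical analysis section.
3. From that model derive the break-even proportion with its uncertainty, giving surgery prevented, chemotherapy omitted and chemotherapy changed each its own net cost. Compare the confidence interval for prevented curative surgery with it. The other components are estimated in the same patients, so their uncertainty should be carried through jointly.
4. Report the three components separately alongside the composite, each patient in one category.

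The cost is wording plus one calculation in a model already planned. Prevented surgery is already named as a component; the only added coding is to separate omitted from changed chemotherapy. The downside is that the headline percentage tied to cost may be smaller than the composite.

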### Statistical analysis

The primary outcome measures, change in treatment strategy of PET and SL, will be presented as a percentage. To evaluate the performance of PET and SL, sensitivity and specificity will be calculated. A separate analysis will be performed to assess whether both diagnostic modalities are accurate for various subgroups, for instance tumor types (Lauren classification: diffuse, intestinal and mixed). The quality of life of patients in this study will be compared to previous data from literature and to a retrospective cohort of patients who did not undergo PET and SL. Differences are tested using linear mixed-effects modeling, taking relevant patient characteristics into account. Missing values will be imputed using multiple imputation techniques. Statistical significance is defined as *p* < 0.05. Cost-effectiveness will be calculated, taking all relevant health-related costs into account, including costs arising from complications of medical treatment, and additional diagnostics arising from false-positive findings on PET. A model (Fig. 2) will be developed to compare health care costs with only CT. A budget impact analysis (BIA) will be performed, adhering to the newest guidelines and applying the societal, health insurance/third party payer and health care perspectives. Analyses will be performed for the combination of PET and SL and for both treatment modalities separately.

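### The study is sized to demonstrate at least 22% at alpha 0.05 and power 0.80, but the stated primary analysis is a bare percentage with no interval, test or sidedness

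*Protocol article*

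**What the plan says.** The Sample size calculation section of the protocol article sets up a hypothesis-test design for one proportion. The expected value comes first: "it is expected that 27% of patients will have a change in treatment strategy". A lower bar follows: "Taking a safety margin of 5% into account (thus at least 22% of patients will have a change in treatment strategy". The error rates are "an alpha of 0.05 and a power of 0.80", and sidedness is not given. The purpose is stated as a claim to be shown: "at least 239 patients need to be included in this study to demonstrate that performing a combination of both diagnostic modalities is cost-effective". The abstract puts the same purpose as break-even: "At least 239 patients need to be included in this study to demonstrate that the diagnostic modalities are break-even". The section also gives the expected recruitment: "approximately 543 patients are expected to be eligible for the study in 36 months".

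The Statistical analysis section says this of the primary outcome: "The primary outcome measures, change in treatment strategy of PET and SL, will be presented as a percentage". The 22% bar does not appear in that section. The section names linear mixed-effects modelling for quality of life, sets a general significance level of p < 0.05, and assigns cost-effectiveness to a decision model and a budget impact analysis.

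**The concern.** Alpha and power are properties of a decision rule. The sample size section quotes both and says that something will be demonstrated, but the analysis section describes a purely descriptive result. A reader cannot tell what event has a 5% chance of occurring wrongly, or what event has an 80% chance of occurring when the true proportion is 27%.

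This matters because the Discussion says the results will be implemented in an updated national guideline. With no rule fixed, an observed proportion somewhat above 22% could be presented as showing that the bar is met although the data are compatible with values below it. The open choice of sidedness could also be settled after the data are seen, and at n=239 that choice can reverse the conclusion for a result right at the study's own expectation.

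**Working it through.** **Inputs.** From Sample size calculation: p1 = 0.27, p0 = 0.27 − 0.05 = 0.22, alpha 0.05, power 0.80, n = 239 (minimum) and n = 543 (expected eligible). Sidedness is not stated, so both are shown.

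**1. The plan's own figure.** The one-sample formula is n = [(z_α·√(p0·q0) + z_β·√(p1·q1)) / (p1 − p0)]², with √(0.22 × 0.78) = 0.4142 and √(0.27 × 0.73) = 0.4440.

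- One-sided: [(1.645 × 0.4142 + 0.8416 × 0.4440) / 0.05]² = 445.2, so 446.
- Two-sided: [(1.960 × 0.4142 + 0.8416 × 0.4440) / 0.05]² = 562.2, so 563.

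Neither gives 239. Continuity-corrected (465 or 582) and arcsine (457 or 580) versions do not either, nor does a confidence-interval half-width of 5 points at 27% (303 at 95%, 214 at 90%). So the test behind 239 cannot be inferred from the number itself. That discrepancy is a separate point; here it means that the sample size does not supply the missing rule.

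**2. If the bare percentage were read against 22%.** This rule is an assumption; the article does not state it. The smallest count giving at least 22% is 53 of 239 (22.2%) or 120 of 543 (22.1%). Exact binomial probabilities of reaching it:

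| n | Count needed | True 22% | True 20% |
|---|---|---|---|
| 239 | 53 | 0.499 | 0.222 |
| 543 | 120 | 0.494 | 0.122 |

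If the percentage were instead read against 27% (65 of 239), the probability would be 0.034 at a true 22% and 0.497 at a true 27%. Neither reading gives 0.05 together with 0.80.

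**3. If the lower confidence limit must exceed 22%.** Exact binomial error and power of that rule:

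| n | Rule | Count needed | Error at true 22% | Power at true 27% |
|---|---|---|---|---|
| 239 | one-sided 5% | 64 (26.8%) | 0.046 | 0.555 |
| 239 | two-sided 95% | 66 (27.6%) | 0.024 | 0.439 |
| 543 | one-sided 5% | 136 (25.0%) | 0.0499 | 0.859 |
| 543 | two-sided 95%, exact limit | 140 (25.8%) | 0.020 | 0.753 |
| 543 | two-sided 95%, Wilson limit | 139 (25.6%) | 0.026 | 0.783 |

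Except in the last two rows, Wilson and exact limits require the same count.

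**4. Does the open choice matter for a plausible result?** Take 65 of 239 = 27.2%, essentially the hypothesised value. The Wilson lower limit is [p + z²/2n − z·√(p·q/n + z²/4n²)] / (1 + z²/n).

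- z = 1.960: (0.2720 + 0.0080 − 0.0570) / 1.0161 = 0.2195, shown as 21.9% when cut to one decimal. This is below 22%.
- z = 1.645: 22.7%. This is above 22%.

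The same on-target data fail one version of alpha 0.05 and pass the other.

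**The case against.** The strongest reply is that this is a condensed article. Presenting a percentage does not exclude a confidence interval, and the interval method is often left to a full protocol or analysis plan, which is not shown. The section also sets p < 0.05 in general, matching the alpha in the sample size section. Moreover, cost-effectiveness is to be judged by a decision model and a budget impact analysis, not by the percentage alone.

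Part of this stands. The absence of an interval formula would not be a finding by itself, and passing 22% would not in itself establish cost-effectiveness. But the article does use its analysis section to state the primary analysis, and what it states is descriptive, while the sample size section ties alpha, power and a demonstration to this same proportion. The general p < 0.05 line names no test against 22%.

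A reader might also infer that the plan adopts a point-estimate pass rule with a type I error near 50%. The document does not support that. It nowhere says that success is declared when the observed percentage reaches 22% or any other value. The 0.499 belongs to one assumed rule, any rule that passes at the null value errs about half the time whatever the study, and a 27% rule would give 3.4%. Nor does the point need a centre-robust standard error: the article gives no between-centre correlation, so that is an optional refinement.

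**Conclusion.** The point holds as a mismatch between two sections. The study is sized to demonstrate at least 22% at alpha 0.05 and power 0.80, but the stated primary analysis contains no interval, no test against 22% and no sidedness, so those error rates attach to no stated analysis.

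The size depends on what fills the gap. The chance of wrongly clearing the bar at a true 22% is about one half if the bare percentage is read against 22%, and at or close to the nominal level if a lower limit is used. For 65 of 239 the choice of sidedness alone decides the conclusion. The calculations assume independent patients, a single binomial proportion, and 239 or 543 patients analysed. They say nothing about whether 22% is the right break-even value. The defect is worth correcting, and it does not invalidate the data collection.

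**What to change.** In Statistical analysis, state that the primary proportion will be reported with a Wilson or exact confidence interval, and that the 22% bar will be claimed as met only if the lower limit exceeds 22%. Name the interval method, since Wilson and exact limits can differ by one patient (139 against 140 at n=543). State the sidedness in both Sample size calculation and Statistical analysis, and fix it before the data are examined.

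The text change is one or two sentences and needs no new data. The real cost is that the power has to be restated. With this rule, n=239 gives about 56% (one-sided 5%) or 44% (two-sided 95%) at a true 27%, not 80%. At n=543 it gives about 86%, or 75% to 78% depending on the interval method. An observed proportion modestly above 22% would also no longer count as proof.
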